**Methods:**

The TALKING TIME study is a randomized controlled trial. The effects of the 3-month TALKING TIME intervention will be compared with those of a control group without intervention at two time points (baseline = T_0_, after 3 months = T_1_). The control group will receive the TALKING TIME intervention after T_1_. With a planned sample size of 88 participants, the study is powered to detect an estimated effect size of 0.70 for psychological quality of life, considering an α of 0.05 (two-sided), a power of 80%. Caregivers are informal caregivers who are eligible if they are 18 years of age or older and have cared for a person with diagnosed dementia for at least four hours, four days per week, in the past six months. The exclusion criteria are psychiatric disorders of the informal caregiver. The primary outcome is the mental component summary of the SF-12 rated by informal caregivers. The secondary outcomes for informal caregivers are the physical component summary of the SF-12, the Perceived Social Support Caregiver Scale (SSCS) score, and the Caregiver Reaction Scale (CRS) score. The secondary outcome for care recipients is the Neuropsychiatric Inventory (NPI-Q). For the process evaluation, different quantitative and qualitative data sources will be collected to address reach, fidelity, dosage and context.

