### Study aim and research question

The aims of this Medical Research Council (MRC) framework phase II trial [27] were translated into the following research question:1.Does the TALKING TIME intervention positively affect the health-related quality of life (HRQoL) of informal caregivers of people with dementia, their perceived social support, and the reaction of the informal caregivers?

To detect possible types of intervention harm for care recipients, a second research question asks the following:2.Does the TALKING TIME intervention affect the challenging behavior of people with dementia who are cared for by an informal caregiver?

Two research questions target the investigation of the study and intervention processes (process evaluation):3.To what extent can the intervention be delivered as planned (degree of implementation)?4.What are the facilitators of and barriers to the TALKING TIME intervention?

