### Measurements

To evaluate the intervention effects and to study the process of intervention implementation, quantitative measurements will be applied. The measurements were chosen based on their appropriateness for the target intervention, sample, data collection procedure (telephone interviews), and psychometric properties. Table 1 summarizes all of the measurements. Because not all measurements will be psychometrically tested in the German context, the internal consistency of all applied measurements will be evaluated as part of the descriptive data analysis.

**Table 1 Tab1:** Measurement instruments

Caregiver				
Variable	Instrument/Source	No. of Items	Measurement	Type of Variable
Self-rated mental health	Mental Component Summary (MCS) of the General Health Survey Questionnaire Short Form 12 (SF-12) [4, 33]	6	T_0_ – T_1_	Primary outcome
Self-rated physical health	Physical Component Summary (PCS) of the General Health Survey Questionnaire Short Form 12 (SF-12) [4, 33]	6	T_0_ – T_1_	Secondary outcome
Social support	Perceived Social Support Caregiving (PSSC) [35]	9	T_0_ – T_1_	Secondary outcome
Social conflict	Perceived Social Conflict Scale (SCS) [35]	3		Control variable
Caregiver reaction	Caregiver Reaction Scale (CRS) [38–40]	24	T_0_ – T_1_	Secondary outcome
Education level	Consortium to Establish a Registry for Alzheimer’s Disease (CERAD) [46]	2	T_0_	Control variable
Demographic variables	Single items	16	T_0_ – T_1_	Control variables
Care Recipient				
Variable	Instrument/Source	No. of Items	Measurement	Type of Variable
Cognition	General Practitioner Assessment of Cognition (GPCOG) [42, 43]	6	T_0_ – T_1_	Control variable
Activities of daily Living	Functional Activities Questionnaire [44, 45]	10	T_0_ – T_1_	Control variable
Challenging behavior	Neuropsychiatric Inventory – Q [41]	12	T_0_ – T_1_	Secondary outcome
Demographic variables	Single items, e.g., age, gender, care dependency (care recipient)	22	T_0_ – T_1_	Control variables
Process Evaluation				
Variable	Instrument (Source)	Measurement		Process Evaluation Domain
Recruitment strategies	Process documents of the TALKING TME study	T_0_		Reach
Numbers of interested, refused, rejected, and included informal caregivers	Process documents of the TALKING TIME study Single items (T0) and process documents of the TALKING TIME study	Ongoing^1^		
Randomization	Process documents of the TALKING TIME study	Ongoing		
Dropouts	Process documents of the TALKING TIME study	Ongoing		

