### Effect evaluation

The primary outcome is the mental component summary (MCS) of the General Health Survey Questionnaire Short Form 12 (SF-12) [4, 33]. The SF-12 is widely used and has shown its feasibility in telephone interviews [33]. Depending on the items, two, three, five, or six response options are available. The items show different scale levels: two, three, five, or six response categories. The MCS consists of six items that assess mental HRQoL. The total score ranges from 0 to 100.

The secondary outcomes for informal caregivers are self-rated physical HRQoL, social support, social conflict, and caregiver reaction, as well as the proxy-rated challenging behavior of care recipients with dementia. Physical HRQoL will be assessed with the second domain of the SF-12, the physical component summary (PCS). The PCS also consists of six items with scores ranging from 0 to 100. Higher scores of the MCS and the PCS correspond to higher HRQoL values. Both SF-12 component scores have shown adequate reliability and validity [34].

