## Data analysis

### Effect analysis

The primary and secondary outcomes from the intervention and control groups will be compared using descriptive and advanced statistical methods at T_0_ and T_1_. A mixed effect model will be computed to evaluate the differences between the intervention and control groups regarding the development of primary and all secondary outcomes during the study period (T_1_). The mixed effect model will account for the repeated measurements of the participants. Additionally, a model for evaluating the impact of the between cluster differences will be tested by including the clusters as random effects. A cluster is defined as a group of a maximum of four informal caregivers who represent the members of one support group. To evaluate the effect of the assignment, the intention to treat principle (ITT) will be applied. The results of the ITT will be compared to a per protocol analysis to assess the effect of intervention adherence. In all analytical steps, the effect estimates will be adjusted for baseline differences and differences in the control variables at all measurement points. The mixed effect model for the primary outcome will also consider the secondary outcomes as control variables. A statistician who is blinded to group allocation will perform the statistical analyses. The research team members responsible for the effect evaluation will be blinded to the results of the process evaluation until the final mixed effect model for the primary outcome is computed.

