### Study progress

The study design and protocol were approved by the Ethics Committee of the University of Leipzig in February 2016 (Register number: 052/16-ek). The recruitment began in March 2016 and collection of informed consent began in June 2016. The assessment of baseline data for the first support group cluster began in July 2016. The last T_1_ measurement, effect, and process evaluations are scheduled for March 2017. Analysis of the data and the dissemination of the results are planned for summer 2017.

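### The effect team's blind to process results ends at the primary-outcome model; it should last until the secondary models, including the NPI-Q harm model, are final

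*Protocol article*

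**What the plan says.** The protocol article, Effect analysis, separates the team members who evaluate effects from the process evaluation. They "will be blinded to the results of the process evaluation until the final mixed effect model for the primary outcome is computed". Earlier in the same paragraph, the mixed model is planned to compare the groups "regarding the development of primary and all secondary outcomes during the study period". The paragraph also states: "A statistician who is blinded to group allocation will perform the statistical analyses". One adjustment rule, for baseline differences and the control variables, applies at every analytical step.

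Under Study aim and research question, the second question concerns harm to care recipients: "Does the TALKING TIME intervention affect the challenging behavior of people with dementia who are cared for by an informal caregiver". It is answered through the NPI-Q, a secondary outcome.

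The list of secondary outcomes differs between sections. Effect evaluation states: "The secondary outcomes for informal caregivers are self-rated physical HRQoL, social support, social conflict, and caregiver reaction, as well as the proxy-rated challenging behavior". The abstract's list for caregivers is "the physical component summary of the SF-12, the Perceived Social Support Caregiver Scale (SSCS) score, and the Caregiver Reaction Scale (CRS) score", without social conflict. Table 1 classes the social conflict scale (SCS) as a control variable.

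On timing, Study progress says: "The last T_1_ measurement, effect, and process evaluations are scheduled for March 2017". The sentence after it places data analysis and dissemination in summer 2017.

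**The concern.** The blind exists so that knowing how well the groups ran, who attended and how satisfied participants were cannot steer the modelling of effects. The article gives it an explicit end point, and that end point names only the primary outcome. This is a stated rule, so it is not a detail left to an analysis plan that is not shown.

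The models outside the rule carry much of the trial's stated purpose. The first research question has three parts: health-related quality of life, perceived social support and caregiver reaction. The last two rest wholly on secondary outcomes. The second question, on harm, rests on the NPI-Q. If process results reach the effect team before these models are fixed, choices among covariates or between model versions could be made with that knowledge.

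**Working it through.** No sample size, error rate or estimate in the article depends on this point, so there is no figure to reproduce. The check is a count of the scores involved and a comparison of passages.

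**Step 1: which models the blind names.** Effect analysis names one, the final model for the SF-12 mental component summary. No section extends the blind to the secondary models, and none says that they are finalised together with the primary model.

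**Step 2: how many scores lie outside it.** Inputs are the abstract, Table 1 and Effect evaluation. The caregiver reaction scale (CRS) is scored by subscale; its item counts 7 + 5 + 3 + 5 + 4 = 24 match the stated total, which gives five scores.

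| Score | Table 1 and abstract | Effect evaluation text |
|---|---|---|
| SF-12 physical component | 1 | 1 |
| Perceived social support (PSSC) | 1 | 1 |
| CRS subscales | 5 | 5 |
| NPI-Q | 1 | 1 |
| Social conflict (SCS) | 0 | 1 |
| **Total** | **8** | **9** |

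With the CRS counted as one construct, the totals are 4 and 5. The NPI-Q is included under every count.

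**Step 3: how much freedom is left in those models.** The model type and the adjustment rule are common to all outcomes, which narrows the choice. Three things keep it from closing:
- The pool of control variables is broad. Table 1 lists 16 caregiver and 22 care-recipient demographic items, plus education, cognition, daily activities and social conflict.
- Adjustment for baseline differences does not name which differences will enter.
- A further model with clusters as random effects is to be examined in addition to the repeated-measures model.

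**Step 4: what process results could reveal.** Controls receive no component of the intervention until after T1 (Control group). Attendance and adherence in the sessions held before T1 therefore concern treated participants only. Process analysis works through each intervention cluster in turn, and Table 1 lists randomization and dropouts among the process variables. Results in that form could weaken the statistician's allocation blind. Whether they would depends on how they are reported, which the article does not say.

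**Step 5: timing.** The March 2017 entry groups the last measurement with both evaluations, so process results may exist by the time models are fitted. Process analysis also sets a milestone after the first three clusters, of eleven planned, so some results may exist earlier. Neither statement fixes an order between process results and secondary models.

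**The case against.** The strongest reply is that the main safeguard covers every outcome. The statistician is blinded to allocation (Design and Effect analysis), and the article prescribes one modelling approach and one adjustment rule throughout. A reader might infer that only the primary model is protected and that every other model is open. The documents do not support that: a single additional layer, the blind to process results, ends early, while the allocation blind stays in place for all models.

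A reader might also infer that the plan schedules the secondary models after process results are released. It does not. The March 2017 entry may refer to data collection, and the analysis itself is placed in summer 2017. Exposure is permitted, not planned. It would likewise go too far to say that nine models are affected, because that count needs social conflict to be secondary, which Table 1 and the abstract do not support.

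A third tempting reading is that letting process results inform the judgement of harm is itself a defect. The Discussion intends exactly that: harm is to be assessed from the outcomes together with the process evaluation. Only the building of the models is at issue, not their later interpretation.

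Finally, this is a phase II trial preparing a later one, and limiting an extra safeguard to the primary outcome can be a deliberate choice. That bears on the weight of the point. It does not give a reason to stop the blind at the primary model when carrying it further costs so little.

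**Conclusion.** The point holds in a limited form. As written, the rule lets the effect team learn process results while eight or nine secondary scores, the NPI-Q among them, may still be open to modelling choices. The allocation-blinded statistician and the common model rule reduce the risk without removing it.

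This rests on three assumptions: that the secondary models may be finalised later than the primary one; that process results would reach people who build or advise on those models; and that those results concern sessions held before T1. The article does not exclude any of these and does not establish them.

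The importance is modest. The primary analysis is unaffected, no stated figure changes, and neither the size nor the direction of any bias can be computed from the document. It is worth raising because the remedy is cheap and the outcomes concerned answer most of the first research question and all of the second.

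**What to change.** Replace the end point of the blind with one that covers all effect models: the effect team stays blind to process results until the final intention-to-treat models for the primary and all secondary outcomes have been computed and locked. Process results are then released for the per-protocol comparison, which needs adherence data, and for the interpretation of harm that the Discussion intends.

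So that the new sentence has a definite scope, state once whether social conflict is a secondary outcome or a control variable, and align the abstract, Table 1 and Effect evaluation.

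The cost is one changed sentence, one consistency correction and a short delay in releasing process results to the effect team while the remaining models are run. Data collection and sample size do not change.

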### Process analysis

The process evaluation data will be analyzed using descriptive statistical methods. Following an analysis of the data set of each intervention cluster, the results for each cluster will be synthesized in a side by side comparison. The members of the research team responsible for the process evaluation will be blinded to the effectiveness results until the completion of the process evaluation for the first three clusters.

### Study progress

The study design and protocol were approved by the Ethics Committee of the University of Leipzig in February 2016 (Register number: 052/16-ek). The recruitment began in March 2016 and collection of informed consent began in June 2016. The assessment of baseline data for the first support group cluster began in July 2016. The last T_1_ measurement, effect, and process evaluations are scheduled for March 2017. Analysis of the data and the dissemination of the results are planned for summer 2017.

## Discussion

This randomized controlled trial will provide important information on the effectiveness of the TALKING TIME intervention as a structured telephone-based support group for informal caregivers of people with dementia and knowledge on the effective and ineffective intervention components and trial procedures (e.g., sample recruitment).

Previous studies investigating supportive interventions for informal caregivers have demonstrated no risks for participants (Dam et al. [9]). However, based on the measurement of the primary and secondary outcomes for informal caregivers and people with dementia, as well as the process evaluation, this trial allows a comprehensive evaluation of the types of intervention harm. In summary, the study findings will be an important basis for the design of a subsequent randomized controlled trial in the third phase of the MRC framework [27].

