### Sample size calculation

The sample size calculation is based on the effect size of the primary outcome, the “mental component” of the HRQoL. A meta-analysis demonstrated an effect size of 2.03 (95% Confidence Interval 1.36 to 2.70) for SWB in support groups but only measured in one single trial [6]. We assume a more conservative effect size of 0.70. This effect size was chosen on the basis of the findings of the study „German Adaptation of REACH II“(GE-REACH) [28], which yielded an effect size between 0.57 (post) and 0.89 (follow-up), thus on average 0.73, for the outcome SWB, measured with mental component summary (MCS) of the General Health Survey Questionnaire Short Form 12 (SF-12). The randomization will be performed on the individual participant level within predefined clusters; a conservative sample size calculation based on a parallel design is computed. A significance level of α of 0.05 (two sided) and a power of 80% for psychological QoL results in a target sample size of 68 participants (34 in each group). An estimated dropout rate of 20% [29] will raise the sample size to 86 study participants. The clusters with eight informal caregivers each lead to a further increase of the sample to 88 informal caregivers (eleven clusters with eight participants each). Therefore, we plan to include 88 informal caregivers in the TALKING TIME study.

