Caregiver reaction will be rated with the caregiver reaction scale (CRS) [38–40]. This measurement contains 24 items reflecting caregiver self-esteem (7 items, range: 7 to 35), a lack of family support (5 items, range: 5 to 25), the impact of finances (3 items, range: 3 to 15), the impact of the daily schedule (5 items, range 5 to 25), and the impact on health (4 items, range: 4 to 20). Based on the recommendation of Given et al. [38], we compute the subscale scores, with higher scores indicating a stronger impact. The German version of the CRS has demonstrated sufficient internal consistency and structural validity [39].

The challenging behavior of care recipients will also be assessed as a secondary outcome based on a proxy rating using the Neuropsychiatric Inventory-Q (NPI-Q) [41]. This measurement makes it possible to assess the presence and severity of the following 12 different behaviors and psychological symptoms related to dementia: 1. delusion, 2. hallucination, 3. depression, 4. anxiety, 5. euphoria, 6. aggression, 7. apathy, 8. disinhibition, 9. irritability, 10. aberrant motor behavior, 11. sleep problems, and 12. eating disorders. The severity of the behaviors and psychological symptoms is assessed based on the response options of mild, moderate, and severe. The measurement results in a total score ranging from 0 to 36, with higher scores indicating more challenging behavior. The NPI-Q has shown adequate reliability and validity [41].

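### The claim of a comprehensive evaluation of types of harm goes further than a caregiver-rated NPI-Q total and descriptive process data can support

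*Protocol article*

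**What the plan says.** The section on study aim and research question introduces research question 2 with a harm purpose: "To detect possible types of intervention harm for care recipients, a second research question asks the following". The question itself is neutral. It asks whether the intervention affects the challenging behaviour of the person with dementia.

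The measure is the NPI-Q, a proxy rating of the presence and severity of 12 behaviours. On scoring, the Effect evaluation section says: "The measurement results in a total score ranging from 0 to 36, with higher scores indicating more challenging behavior".

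The Effect analysis section handles this outcome like every other: "A mixed effect model will be computed to evaluate the differences between the intervention and control groups", for the primary and all secondary outcomes.

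The Discussion then says, on the basis of the caregiver and care-recipient outcomes together with the process evaluation, that "this trial allows a comprehensive evaluation of the types of intervention harm". It presents the findings as a basis for the next-phase trial.

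**The concern.** Detecting types of harm is one of four research questions, and the Discussion says the trial answers it comprehensively. That is a claim about what the design can do, so it can be checked against the methods in the same article without assuming anything about an unseen analysis plan.

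Three features sit badly with it. The named result is a single sum score, which does not distinguish one type of harm from another. The rater is the caregiver, who knows whether he or she is in a support group. The trial is sized only for a large effect on the SF-12 mental component. If the word comprehensive stands, readers planning the phase III trial may take more reassurance from the harm results than the data can give.

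**Working it through.** **1. The plan's own sample size.** Inputs from the Sample size calculation section: a two-sided test at 0.05 with 80% power; for the effect, "We assume a more conservative effect size of 0.70"; 34 evaluable caregivers per arm, 68 in all; and a 20% allowance for dropout that takes the total to 86.

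- Normal approximation: n per arm = 2 × (1.960 + 0.842)² / 0.70² = 15.70 / 0.49 = 32.04, so 33.
- Noncentral t: power is 0.7997 with 33 per arm and 0.812 with 34, so 34 per arm, or 68 in total.
- Dropout: 34 / 0.8 = 42.5, so 43 per arm, or 86. The next multiple of 8 is 88.

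The figures 68, 86 and 88 all reproduce. They refer to the SF-12 mental component only. No calculation is given for the NPI-Q.

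**2. What the total can show.** Twelve items at three severity levels give 12 × 3 = 36, which matches the stated range if an absent symptom scores 0. Suppose one care recipient's aggression goes from mild to severe (+2) and apathy from severe to mild (−2). The total changes by 0, although one symptom is clearly worse. The item data that would show this are collected, but the article names only the total as the result.

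**3. Who rates, and who can be rated.** The Design section blinds the statistician and the data collectors. The NPI-Q rating comes from the caregiver. The Control group section gives controls no component until after T1, so caregivers can tell their arm. One session theme is about interacting better with the relative, so a changed rating may partly reflect changed perception. A pair truly lost before T1 has no follow-up NPI-Q. After T1 the controls receive the intervention, so no later comparison with an untreated control group is available.

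**4. What the process evaluation adds.** It covers reach, fidelity, dosage and context. It includes the number of dropouts and their reasons, moderator records for each session and a participant questionnaire after each session. The Process analysis section describes descriptive methods and a side-by-side synthesis of clusters. Before T1, session records can exist only for the intervention arm. These sources can raise a signal, but the session records cannot be compared between arms.

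**5. Precision of the NPI-Q difference.** The article gives no NPI-Q standard deviation, so results are in SD units, with 34 evaluable per arm.

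- Standard error, unadjusted: √(2/34) = 0.2425 SD.
- 95% half-width: t(0.975; 66 df) × 0.2425 = 1.997 × 0.2425 = 0.48 SD.
- With baseline adjustment, normal quantile: 1.96 × 0.2425 × √(1 − r²). For r = 0.5 this is 0.475 × 0.866 = 0.41 SD; for r = 0.7 it is 0.475 × 0.714 = 0.34 SD. Both correlations are assumptions.

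| True worsening | Power, unadjusted (noncentral t) |
|---|---|
| 0.2 SD | 13% |
| 0.3 SD | 23% |
| 0.4 SD | 37% |
| 0.5 SD | 53% |

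With adjustment, power at 0.3 SD (normal approximation) is about 30% for r = 0.5 and 41% for r = 0.7. The difference detectable with 80% power is 0.68 SD unadjusted, and 0.59 or 0.49 SD adjusted for r = 0.5 or 0.7.

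An observed difference of exactly zero would therefore still be compatible with a worsening of up to 0.48 SD (0.34 to 0.41 SD adjusted). A non-significant estimate on the side of worsening would leave room for more.

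**The case against.** The strongest reply has four parts.

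- **Other sources.** The Discussion does not rest harm on mean scores alone. The same sentence brings in the process evaluation, with dropout reasons and session-level records. A reader might infer that harm is judged only from group means of those interviewed at T1; the text does not support that. This part stands.
- **No rule on null results.** A reader might also infer that a non-significant NPI-Q difference will be taken as proof of safety. No such rule, margin or non-inferiority claim is written. This part also stands.
- **Detail left to other documents.** Item tables, intervals and adverse-event procedures are what a condensed article commonly leaves to the full protocol or analysis plan. Their absence is not charged here. But the article does state a property of the design, and that statement has to fit the methods it describes.
- **Size and phase.** The half-width of 0.48 SD ignores the planned baseline adjustment. With a correlation of 0.7, a 0.5 SD worsening would be detected with slightly more than 80% power. Limited precision is normal in a phase II trial, and giving controls later access is a reasoned choice to keep them in data collection. This narrows the precision argument but does not make a total score informative about types of harm.

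It is also fair that the article does not say caregivers who stop attending are not interviewed at T1. Intention-to-treat is planned, so leaving the groups should not be equated with having no T1 score.

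**Conclusion.** The point holds as an overstatement. Research question 2 and the Discussion speak of types of harm, while the described care-recipient result is one proxy-rated total that cannot separate them. The process data are descriptive, and the session records before T1 are one-armed.

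Precision supports the same conclusion. Small worsening would usually be missed. Whether a 0.5 SD worsening would be missed depends on the assumed T0–T1 correlation: power is about 53% without adjustment and slightly above 80% with adjustment at r = 0.7. These figures assume 34 evaluable per arm, equal variances and no allowance for clustering. Using 35 per arm (88 / 2 × 0.8 = 35.2) leaves the unadjusted half-width at 0.48 SD.

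Severity is minor. The primary analysis, the sample size and the data to be collected are unaffected.

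**What to change.** Using data already planned:

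1. For research question 2, tabulate by arm the number of care recipients with a new or more severe symptom on each of the 12 NPI-Q items from T0 to T1.
2. Beside it, give the between-group difference in the NPI-Q total with its 95% interval, and the dropouts with reasons by arm.
3. State that a non-significant NPI-Q difference is not evidence of no harm.
4. In the Discussion, describe the harm evaluation as an exploratory, mainly caregiver-rated assessment up to 3 months, in place of a comprehensive one.

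The item table is the change that matters most, because it lets the trial speak about types of harm. Item 2 is mostly detail that could sit in the analysis plan. The item ratings still come from caregivers who know their arm, so the table does not remove rating bias; the new wording should make that plain. The cost is a few descriptive tables and a less reassuring harm statement. No new data or participants are needed.
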